## Abstract

**Background:**

It is hypothesized that the grieving process of relatives of missing persons is complicated by having to deal with uncertainty about the fate of their loved one. We developed a cognitive behavioural therapy (CBT) with mindfulness that focuses on dealing with this uncertainty. In this article, we elucidate the rationale of a pilot randomised controlled trial (RCT) for testing the feasibility and potential effectiveness of this CBT for reducing symptoms of psychopathology in relatives of missing persons.

**Methods:**

A pilot RCT comparing participants of the CBT condition (*n* = 15) with waiting list controls (*n* = 15) will be executed. Individuals suffering from psychopathology related to the long-term disappearance of a loved one are eligible to participate. The treatment consists of eight individual sessions. Questionnaires tapping psychological constructs will be administered before, during, and after the treatment. The feasibility of the treatment will be evaluated using descriptive statistics (e.g., attrition rate). The primary analysis consists of a within-group analysis of changes in mean scores of persistent complex bereavement disorder from baseline to immediately post-treatment and follow-up (12 and 24 weeks post-treatment).

**Discussion:**

A significant number of people experience the disappearance of a loved one. Surprisingly, an RCT to evaluate a treatment for psychopathology among relatives of missing persons has never been conducted. Knowledge about treatment effects is needed to improve treatment options for those in need of help. The strengths of this study are the development of a tailored treatment for relatives of missing persons and the use of a pilot design before exposing a large sample to a treatment that has yet to be evaluated. Future research could benefit from the results of this study.

**Trial registration:**

NTR4732 (The Netherlands National Trial Register (NTR))

## Background

The disappearance of a significant other is a potentially devastating loss, due to the lack of knowledge whether the disappeared is dead or alive. Research on the psychological consequences for relatives of the disappeared is scarce and has mainly been conducted in the context of armed conflicts [1–8]. These studies indicate that the disappearance of a significant other is associated with elevated levels of post-traumatic stress disorder (PTSD), major depressive disorder (MDD), and/or disturbed grief.

### Grief following the death or disappearance of a loved one

Whereas little is known about emotional consequences of disappearance, there is a large body of knowledge about both uncomplicated and disturbed grief after the death of a loved one. Grief after the death of a loved one is typically characterized by transient sadness, preoccupation with the circumstances surrounding the loss, and longing for the deceased [9]. People mostly adapt well to the death of a significant other. Nonetheless, about 10 % of the bereaved experience disturbed grief [10, 11]. When grief complaints persist or increase at least 6 months post loss and are associated with distress and impairments in daily functioning, it can be defined as complicated grief (also referred to as prolonged grief disorder) [12]. Although complicated grief partly overlaps with PTSD and MDD, research has shown that these disorders are distinguishable (for overview see [13]). Persistent complex bereavement disorder (PCBD) was included in the fifth edition of the Diagnostic and Statistical Manual of Mental Disorders (DSM-5) as condition for further study [14]. PCBD encompasses persistent separation distress, preoccupation with the loss and the circumstances of the loss beyond 12 months after the loss [14].

There are at least three reasons to assume that grieving the loss of a disappeared relative is more complex and longer lasting than grieving the loss of a deceased relative. To begin with, the on-going uncertainty about the fate of the missing person may lead to preoccupations with his/her potential whereabouts [2, 15]. Constantly thinking about the missing person may exacerbate negative emotions, interfere with daily life tasks and lead to exhaustion [7, 15, 16]. In addition, families of the disappeared are often confronted with financial, emotional, and practical issues for which they receive little professional support [2, 15]. Finally, family conflicts, social marginalization and a lack of social support from the community have been considered to increase the psychological burden [6, 7].

Taken together, compared to individuals bereaved by the death of a loved one, relatives of missing persons might experience more severe PTSD, MDD, and disturbed grief (henceforth referred to as PCBD operationalized as complicated grief). To the best of our knowledge, this hypothesis was tested in only four quantitative studies [3, 5, 6, 17] and was confirmed in two of them [5, 6]. For example, a study among women with unconfirmed and confirmed loss of their husband in a war-related context showed that the former group was more at risk to experience severe MDD symptoms compared to the latter group [5]. In contrast, two other studies did not show significant differences in the severity of symptoms of psychopathology [3, 17]. For example, relatives of Colombians who had disappeared or died in an armed conflict reported similar levels of PCBD, MDD, and PTSD symptoms [3].

There are reasons for doubting that the results of these studies are applicable to relatives of missing persons in general. Firstly, all four studies were conducted in the context of armed conflicts. The participants were highly traumatized by different war-related stressors (e.g., torture). It might therefore be difficult to distinguish the effect of the disappearance from the effects of other traumatic events. Secondly, the studies were conducted in non-Western samples. In general, cultures may differ in how to deal with loss, but more specifically in how to deal with relatives of missing persons [7]. Finally, there is preliminary evidence that relatives who have more hope that their loved one is still alive also experience more severe PCBD complaints [3]. Within the context of war-related disappearances, the majority of the relatives reported being convinced that their loved one was dead [3, 6]. Therefore, relatives who assume that the disappeared person is dead might suffer less from psychological distress than those who assume that the disappeared person might still be alive. Nevertheless, these comparative studies and other studies [2, 4, 7, 8] show that relatives of missing persons might be susceptible for developing symptoms of PCBD, MDD, and PTSD.

One important step would be to design and evaluate an intervention to target these psychopathological symptoms. To the best of our knowledge, this was only done once; a controlled trial compared the effectiveness of two cognitive behavioural therapy (CBT)-based interventions among women who lost a husband due to death or to disappearance during the Srebrenica massacre [18]. Small to medium pre- to post-treatment effect sizes for both conditions were found for disturbed grief and PTSD. However, the methodological drawbacks of this study, including non-random allocation of participants and lack of a threshold of severity of psychopathology as inclusion criterion, need to be taken into account when interpreting the results. Nevertheless, CBT is the treatment of choice for bereavement-related psychopathology [19]. CBT might therefore also be effective in the treatment of psychopathology among relatives of missing persons.

### CBT for relatives of missing persons

A cognitive behavioural theory of PCBD offers a framework for determining variables that should be targeted in CBT among persons who developed PCBD following the death of a significant other [20]. This and several other theories about PCBD highlight the important role of negative cognitions and maladaptive behavioural strategies in the development and persistence of PCBD [20–22]. Cognitive variables include negative views on the self (“I am worthless since he/she died”) and life (“My life has no purpose since he/she died”), a pessimistic view on the future (“I don’t have confidence in the future”), and catastrophic meanings assigned to one’s own reactions to the loss (“If I would elaborate on my feelings, I would lose control”). Maladaptive behavioural strategies include anxious avoidance and depressive avoidance [20]. The former refers to the avoidance of loss-related stimuli out of fear that confrontation with these stimuli will be unbearable. The latter refers to withdrawal from social, recreational, educational, and/or occupational activities fuelled by the belief that these activities are pointless and/or unfulfilling. Problems with integration of the loss into the autobiographical memory are also associated with PCBD. This results in easily triggered intrusive thoughts, images, and memories upon confrontation with loss-related stimuli [20]. Studies among bereaved individuals suffering from PCBD showed the beneficial effect of targeting these cognitive and behavioural variables using CBT [23, 24].

In addition, symptoms of PCBD have been associated with rumination [25, 26]. Rumination encompasses repetitive thinking about one’s negative feelings, their consequences, and/or antecedents [27]. As the disappearance of a person is surrounded by uncertainties, all kinds of repetitive thoughts (e.g., about the whereabouts of the missing person), including ruminative thoughts (e.g., “What am I doing to deserve this?”), might add to the exacerbation and maintenance of symptoms of psychopathology among relatives of missing persons [3, 7, 15, 16]. Rumination can be regarded as a form of “maladaptive coping”, i.e., an unproductive way to master the consequences of the disappearance. Other forms of maladaptive coping that may be pertinent to recovery from the disappearance of a loved one include substance use and suppression of unwanted thoughts and memories.

Although never studied systematically, it is conceivable that these cognitive and behavioural variables are also involved in the maintenance of psychopathology among relatives of missing persons. For instance, relatives of missing persons might no longer perceive the world as a safe place. As a result, they may experience a reduced sense of control and elevated vulnerability. This poses threats to the view of themselves, life, and the future [2, 16]. Relatives may tend to get preoccupied with the missing person and get entangled in repetitive negative thinking and intrusive memories [2, 3, 5, 16]. Consequently, they could withdraw from previously fulfilling activities. Hoping to find the missing person and at the same time coming to terms with the disappearance can result in conflicting feelings [28]. Holding on to hope that the loved one will return might be used as an avoidance strategy to cope with emotions associated with the thought that the separation is permanent [16]. Some avoid discussing what might have happened to the missing loved one, fearing that this may be perceived as giving up hope [29]. Active searching may therefore provide distraction from dwelling on the worst-case scenarios [28].

CBT could give relatives of missing persons insights into how cognitive processes (e.g., thoughts about how they should have prevented the disappearance) affect their emotions (e.g., sadness) and behaviour (e.g., withdrawing from social activities). Unlike treatment for bereavement-related psychopathology, an intervention for relatives of missing persons should not be primarily focused on closure or coming to terms with the irreversibility of the loss. Instead, this treatment ought to be focused on tolerating the ambiguity surrounding the loss and maladaptive repetitive thinking, including thoughts about the whereabouts of the missing person [7, 30]. Adding elements of mindfulness to CBT might serve this treatment aim. In contrast to focusing on external events (e.g., finding out what happened to the missing person), mindfulness is focused on inner psychological experiences (e.g., one’s thoughts, sensations and feelings). Furthermore, mindfulness is not focused on the past or future, but on the present [31]. Mindfulness-based therapy aims to increase the patient’s awareness of his/her inner thoughts, feelings, and bodily sensations in a non-judgemental way through the practice of training in mindfulness meditation [31]. It has frequently shown to reduce levels of psychopathology [32]. A systematic review showed that the beneficial effect of CBT with mindfulness might be, among other variables, due to the reductions of repetitive negative thinking and enhancement of self-compassion [33]. Self-compassion can be viewed as an emotion-regulation strategy [34, 35] that could play a protective role by preventing to become entangled in negative thoughts and emotions [36]. Although these mindfulness-based cognitive therapies have been tested mainly among persons with recurrent depression, preliminary results showed that this approach could also be effective in treatment of grief-related psychopathology [37, 38].

### Study objectives

The aim of this pilot study is to evaluate the feasibility and the potential effectiveness of CBT with elements of mindfulness in reducing PCBD, MDD, and PTSD symptoms and enhancing the extent of mindfulness among relatives of missing persons. Based on previous studies, we expect that the treatment effect will be mediated by changes in negative cognitive and behavioural variables plus enhancement of self-compassion.

The feasibility of the pilot RCT will be explored by the evaluation of the (1) specifics of potential participation bias, (2) attrition rate, (3) methods used and study design, (4) treatment fidelity, and (5) strengths and suggestions for improvements of the treatment from the perspective of the participant. The primary objective of the analysis of the pilot RCT is to assess changes in mean scores on a measure of PCBD from baseline to 1, 12, and 24 weeks post-treatment. A within-group instead of a between-groups analysis will be executed because this will give the most rigorous information about the potential effects of this treatment given the small sample size.

Secondary objectives of the analysis of the pilot RCT are (1) to evaluate whether the mean scores on measures tapping PCBD, MDD, PTSD, and mindfulness of the treatment group differ from the waiting list control group at the post-treatment/post-waiting period assessment when adjusting for the baseline scores and (2) to test whether the treatment effect is mediated by changes in negative cognitive variables (i.e., reductions in negative grief cognitions, intrusive memories, rumination, and repetitive negative thinking) and behavioural variables (i.e., avoidance behaviours) and enhancement of self-compassion. In addition, the extent of change in repetitive negative thinking, intrusive memories, and self-compassion in response to the treatment will be explored at micro-level by means of tracking measures tapping these constructs during the treatment.

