## Methods

### Design

This is a multi-centre two-arm pilot RCT exploring the feasibility and potential effectiveness of CBT for relatives of missing persons suffering from psychopathology, in comparison with a waiting list control group. The intervention group will start with the treatment within 1 week after randomisation. The waiting list control group will receive the treatment 12 weeks after randomisation. An allocation ratio of 1:1 will be used. The participants will be asked to fill in questionnaires prior to the treatment and 1, 12, and 24 weeks post-treatment. Participants in the waiting list control group will complete an additional questionnaire 1 week prior to their actual start of the treatment. In addition, the participant will be asked to complete a brief questionnaire at the start of each session to assess the potential change in repetitive negative thinking, intrusive memories, and self-compassion during the treatment.

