Randomisation will take place after the participant is screened for eligibility based on the M.I.N.I. Plus and the TGI. A random number generator will be used to perform the blocking randomisation procedure. Relatives of the same missing person will be allocated to the same study arm (i.e., intervention or waiting list condition), in order to prevent transfer of information. An independent researcher will conduct the randomisation procedure. Neither the participants nor the researchers will be blinded. The M.I.N.I. Plus and the Traumatic Grief Interview will be conducted again after the treatment, to examine whether numbers of cases of PCBD, MDD, and PTSD have decreased. The researchers will reimburse costs related to the treatment that are not covered by the respondents’ health insurance. Travel expenses that are related to the visits to the therapist will also be reimbursed (see Fig. 1 for a flowchart of the procedures).

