### Measures

#### Primary outcome measure

##### Inventory of complicated grief

Self-rated symptoms of complicated grief as underlying concept of PCBD will be assessed with the 19-item Inventory of Complicated Grief [44, 45]. Respondents are asked to rate how frequently they experienced 19 grief reactions during the last month, on a 5-point scale ranging from 0 (“never”) to 4 (“always”). The Inventory of Complicated Grief is together with the PG-13 [46] a frequently used instrument to administer grief reactions. Opposed to the former instrument, a validated Dutch translation of the PG-13 is not available. The Dutch translation of the Inventory of Complicated Grief, that demonstrated adequate psychometric properties [45], is therefore chosen as primary outcome measure. We adapted the items of the Inventory of Complicated Grief by referring to the disappearance instead of death (e.g., “Ever since he/she has been missing it is hard for me to trust people”). The Inventory of Complicated Grief is also used as screening instrument in the first part of the screening procedure (see Fig. 1) to assess whether the participant is eligible for the treatment. Participants meet the criteria for PCBD when they score above the cut-off of >25 [44].

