##### Data analyses

Within-subjects repeated measures ANOVA with time (baseline, 1, 12, and 24 weeks post-treatment) as the repeated measure will be performed to evaluate the effects of the treatment in terms of changes in mean scores of PCBD.

Between-subjects multivariate analysis of covariance (MANCOVA) will be performed to compare changes in PCBD, MDD, PTSDD, and mindfulness scores between the treatment and waiting list condition. Specifically, scores at post-treatment (in the treatment condition) and post-waiting period (in the waiting list condition) on measures tapping these phenomena will be compared, including baseline scores as covariates.

Within-subjects MANCOVA with time (baseline, 1, 12, and 24 weeks post-treatment) as the repeated measure will be performed to evaluate the short- and long-term effects of the treatment in terms of change in mean scores of PCBD, MDD, PTSD, and mindfulness. To test whether the treatment effect is mediated by changes in cognitive variables (i.e., grief cognitions, intrusive memories, rumination, and repetitive negative thinking), behavioural variables (i.e., avoidance behaviour), and self-compassion, only the scores of measures tapping these constructs that show the strongest association (based on univariate analyses) will be added to a multiple regression model. Finally, to assess the potential change at micro-level in repetitive negative thinking, intrusive memories and self-compassion throughout the course of the treatment a within-subjects repeated measures ANOVA with time (session 1 to session 8) as the repeated measure will be performed with mean scores of measures tapping repetitive negative thinking, intrusive memories, and self-compassion as outcome measures.

Data will be analysed according to the intention-to-treat principle. Missing data will be handled using multiple imputations. The Statistical Package for the Social Sciences will be used for the analysis. The small sample size of the pilot RCT increases the risk of type II error; the preliminary results regarding the potential effectiveness will therefore be reported with caution following the recommendations for conducting a pilot study [78].

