Strengths of this study are (1) the development of a treatment that is targeted to a specific population, (2) the evaluation of the possible mechanisms of change of the treatment, (3) the inclusion of both an intervention and waiting list control group, (4) the use of a pilot design before exposing a large sample to a treatment that has yet to be evaluated, (5) the assessment of eligibility not only by self-report questionnaires but also with a clinical interview, and (6) the monitoring at micro-level of potential change mechanisms of the treatment. One of the limitations of this study is the lack of power to conduct a multilevel analysis to take into account the nested structure of the data (i.e., repeated measures, nested in individuals, who are, in turn, nested in families or other social systems associated with the same missing person). In addition, the recruitment procedures are focused on a non-treatment seeking population. The percentages of individuals who are willing to participate might therefore be relatively low compared to other studies, and the recruitment of sufficient numbers of participants might therefore be a challenge. Moreover, treatment fidelity will be monitored by methods that rely on self-report which might be prone to bias. Finally, participants whose loved one disappeared less than 12 months earlier can formally not fulfil the criteria of PCBD, because one of the proposed criteria of PCBD is that at least 12 months has elapsed since the loss. The reason for this time frame is to distinguish normal from pathological grief [14]. Because little is known about the grief reactions following the disappearance of a loved one, a shorter time frame is chosen to offer support for those in need of help.

As a result of this pilot study, we may have some evidence whether CBT is effective for relatives of missing persons. Since this is a pilot study, the future results of this study need to be interpreted with caution. The recommendations for the execution of a large-scale RCT based on the results of this pilot study are expected to be relevant for future research. Future intervention studies should verify the results of this study and other possibly effective treatments in order to offer an evidence-based intervention for this population. Taken together, this study will provide the first results of a pilot RCT that evaluates the potential effectiveness of CBT for relatives of missing persons suffering from psychopathology.

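### The primary effectiveness test is an uncontrolled pre-post comparison defended as the most rigorous choice, while the planned randomised comparison is ranked second

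*Protocol article*

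**What the plan says.** The protocol article ranks the analyses the same way in three places.

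- Abstract, Methods: "The primary analysis consists of a within-group analysis of changes in mean scores of persistent complex bereavement disorder from baseline" to post-treatment and follow-up.
- Study objectives: "A within-group instead of a between-groups analysis will be executed because this will give the most rigorous information about the potential effects" of the treatment, given the small sample.
- Data analyses: the repeated measures ANOVA has time (visits at baseline and at weeks 1, 12 and 24 after treatment) "as the repeated measure will be performed to evaluate the effects of the treatment in terms of changes in mean scores of PCBD".

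A concurrent randomised control is measured. Under Design, allocation is 1:1 and "Participants in the waiting list control group will complete an additional questionnaire 1 week prior to their actual start of the treatment"; Table 1 calls this assessment T0.1. The comparison of T1 (CBT arm) with T0.1 (waiting list), adjusted for baseline, is the first secondary objective and appears under Data analyses as a MANCOVA.

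Two further passages bear on the point. The primary outcome scale also helps decide entry: "The Inventory of Complicated Grief is also used as screening instrument in the first part of the screening procedure". On diagnoses, Procedure and randomisation says "The M.I.N.I. Plus and the Traumatic Grief Interview will be conducted again after the treatment, to examine whether numbers of cases" have fallen, and mentions no interview at the end of the waiting period.

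The statistical caution under Data analyses concerns type II error. The Discussion adds a general call for careful interpretation, next to the expectation that "we may have some evidence whether CBT is effective for relatives of missing persons".

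**The concern.** The reason given for the ranking confuses precision with validity. With few participants a between-arm estimate is wide, but it still estimates the effect of CBT against no CBT. A within-group change is narrower because it estimates something else: the effect of CBT plus whatever would have happened anyway.

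Three features of the protocol make untreated change possible. Participants enter because they score above thresholds, one of them on the primary outcome scale. Entry is allowed from just over 3 months after the disappearance. The outcome is an unblinded self-report given repeatedly. Treatment of up to 12 weeks plus 24 weeks of follow-up leaves about 36 weeks for such change.

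A significant time effect could therefore be reported as evidence for the treatment when it shows only that scores fell. Nothing in the article warns the reader that the primary test cannot tell the two apart. The pre-post count of diagnoses has the same weakness.

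**Working it through.** **1. The plan's own figure.** Inputs from Sample size: four time points (m = 4), correlation ρ = 0.50, α = 0.05, power 80%, medium effect. No number is given for medium; I assume Cohen's f = 0.25. For a one-group repeated measures ANOVA under sphericity:

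λ = f² · n · m / (1 − ρ), with df = (m − 1) and (n − 1)(m − 1).

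At n = 24, λ = 0.0625 × 24 × 4 / 0.5 = 12, with df 3 and 69. Power is 81.7%; at n = 23 it is 79.7%. So 24 is the smallest sufficient number, as stated. Adding 19% gives 24 × 1.19 = 28.56, the stated 29; dividing gives 24 / 0.81 = 29.6, or 30, which equals the planned 15 + 15. The sample is thus sized for a time effect in one pooled group, not for a comparison of arms.

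**2. What f = 0.25 means as a change.** Take a fall of d SD by 1 week post-treatment that is held at both follow-ups, so the means are 0, −d, −d, −d. The squared deviations from their mean sum to (3d/4)² + 3(d/4)² = 0.75d². Then f = √(0.75d² / 4) = 0.433d, and f = 0.25 corresponds to d = 0.58.

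**3. The planned test when CBT has no effect.** Let the same pattern arise without any contribution from treatment. Then λ = n × 0.75d² / 0.5 = 1.5nd². The documents give no untreated change, so d is an assumed range.

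| Untreated fall (SD) | λ, n = 24 | Significant, n = 24 | λ, n = 30 | Significant, n = 30 |
|---|---|---|---|---|
| 0 | 0 | 5% | 0 | 5% |
| 0.2 | 1.44 | 14% | 1.80 | 17% |
| 0.3 | 3.24 | 28% | 4.05 | 35% |
| 0.4 | 5.76 | 48% | 7.20 | 58% |

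The rate rises with n, so a larger trial with this primary analysis would make the problem worse.

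**4. The randomised comparison instead.** ANCOVA of the Inventory of Complicated Grief at T1 versus T0.1, with baseline as covariate, r = 0.5 (the plan's correlation) and df = 2n − 3 for n per arm. The expected 95% CI half-width in SD units is t × √((1 − r²) × 2/n).

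- 15 per arm: 2.052 × √(0.75 × 2/15) = 2.052 × 0.316 = 0.65.
- 12 per arm: 2.080 × √(0.75 × 2/12) = 2.080 × 0.354 = 0.74.

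Power for an assumed difference of 0.5 SD uses the noncentrality 0.5/√0.75 × √(n/2). This is 1.58 at 15 per arm (power 33%) and 1.41 at 12 per arm (27%).

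**The case against.** The strongest reply has four parts.

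- **The randomised contrast is already planned.** This stands. A reader might infer from the choice of primary analysis that the control arm is ignored; it is not. The baseline-adjusted comparison is the first secondary objective. The defect lies in its rank and in the reason given for that rank.
- **Untreated improvement is not shown.** This also stands. The Background argues that grief over a disappearance may last longer than grief over a death, and the abstract describes long-term disappearance. A reader might infer that scores are bound to fall without treatment; the documents support only that they may.
- **Regression to the mean is probably modest.** A reader might treat entry as selection on the grief scale alone and expect a large artefact. Entry is through grief, depression and/or PTSD, which weakens selection on any one scale. The effect also depends on whether T0 is the screening questionnaire or a later one; the text does not settle this and Fig. 1 is not shown. I give no figure for it. The upper rows of the table would probably need natural improvement as well.
- **This is a pilot with cautious reporting, and a between-arm test would have little power.** True, but that argues for reporting an estimate with its interval. It does not turn an uncontrolled change into an estimate of treatment effect.

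A reader might also infer that the plan calls type II error its main risk. It says only that the small sample raises that risk.

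**Conclusion.** The point holds as one of ranking, rationale and interpretation. The primary test cannot separate CBT from untreated change, and the small sample does not cure that. If the untreated fall were 0.2 to 0.4 SD, a test with a nominal 5% error rate would be significant in about 14% to 48% of trials at n = 24 and 17% to 58% at n = 30, with no treatment effect. These rates assume sphericity, ρ = 0.5, complete data, the plan's total as n, and a fall complete by 1 week post-treatment and then held. The range of falls is my assumption. The logical flaw does not depend on it.

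The diagnostic counts are likewise uncontrolled as described. A reader might infer that comparing the arms on the screening cut-offs would repair this. It would not: the depression cut-off (>13) marks mild depression, not MDD, and the PTSD screen has an alternative symptom rule beside its cut-off (>38), so the questionnaires do not stand in for interview diagnoses.

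**What to change.** 1. Delete the sentence in Study objectives that calls the within-group analysis the most rigorous.
2. Make the planned between-arm difference in the Inventory of Complicated Grief at T1 versus T0.1 (ANCOVA with baseline score as covariate, 95% CI) the main effectiveness estimate, and base any effectiveness statement on it. Change the Abstract and Data analyses to match.
3. Label the within-group course to 12 and 24 weeks, and the pre-post diagnostic counts, as descriptive and uncontrolled.
4. State under Sample size that the 80% power refers only to the within-group time test, and present the between-arm result as estimation.

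No new participants, visits or measures are needed. The cost is an imprecise headline: a half-width of about 0.65 SD at 15 per arm or 0.74 SD at 12 per arm, and 27% to 33% power for a difference of 0.5 SD. The estimate covers only T1 against T0.1, because the waiting list then receives treatment. The two assessments are also only roughly matched in time: T1 falls 1 week after up to 12 weeks of treatment, T0.1 1 week before a start at week 12. Trial status says recruitment began in January 2015, so the change should be recorded as a dated amendment.
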